**Exclusion criteria**
1. Non-type 1 diabetes (type 2 or monogenic diabetes) and secondary diabetes 2. Pre-existing autoimmune disease (excluding type 1 diabetes) 3. Hypersensitivity to aldesleukin or any of the excipients 4. History of severe cardiac disease (NYHA Class III or IV) 5. History of malignancy within the past 5 years (with the exception of adequately treated basal or squamous cell carcinoma or 2. cervical carcinoma in situ) 6. Clinically significant abnormal laboratory values (out of range and associated with clinical symptoms or signs) in haematology, 2. biochemistry, thyroid, liver and kidney function 7. Pre-existing severe major organ dysfunction or seizure disorders 8. Participation in another clinical trial within 4 months prior to screening 9. Females who are pregnant, lactating or intend to get pregnant during the study 10. Females of childbearing potential who are unwilling or unable to comply with contraceptive advice and regular pregnancy testing 2. throughout the trial 11. Sexually active males who are unwilling or unable to comply with contraceptive advice 12. Current use of immunosuppressive agents or steroids 13. Current treatment with hepatotoxic, nephrotoxic, myelotoxic, or cardiotoxic products 14. Active clinical infections – participants can be recruited after a minimum period of 48-h after the last 2. day of feeling unwell or last day of antibiotic/anti-viral treatment 15. Any medical history or clinically relevant abnormality that is deemed by the principal investigator and/or medical monitor to make 2. the participant ineligible for inclusion because of a safety concern 16. Children with compliance problems (families where the local investigators consider that problems with compliance may be an issue)

### Informed consent

The informed consent form has been approved by the Research Ethics Committee and is in compliance with Good Clinical Practice (GCP), local regulatory requirements and legal requirements. The investigator must ensure that each study participant, or his/her legally acceptable representative, is fully informed about the nature and objectives of the study and possible risks associated with their participation.

The investigator will obtain written informed consent from each patient or the patient’s legally acceptable representative before any study-specific activity is performed. Patients under 16 years of age will be provided with an age-appropriate Patient Information Sheet and will be asked to sign an assent form to document their agreement, and their parents will also be asked to provide consent before the child is allowed to participate. Participants aged 16 years and older will be treated as adults and will be able to consent for themselves. Any participants who turn 16 whilst on study, will be re-consented as an adult at their next study visit. The informed consent form used for this study and any change made during the course of this study, must be prospectively approved by the Research Ethics Committee. The investigator will retain the original of each patient signed informed consent form in patient’s medical notes, a copy will be provided to the patient and one copy kept in the trial site file.

Given the relatively large proportion of trial activities that are carried out within the home setting and the number of home visits, it may not be practical to include families who do not have a sufficient level of English comprehension; this is at the discretion of the local investigator. Should a patient require a verbal translation of the study documentation by a locally approved interpreter/translator, it is the responsibility of the individual investigator to use locally approved translators.

### Randomisation and blinding

Consented participants will be randomly assigned in a 2:1 ratio, to receive treatment with the active drug (aldesleukin) or placebo using a centralised randomisation service, Registration/Randomisation and Management of Product (RRAMP), provided by the Oxford Clinical Trials Research Unit. Randomisation will be computer generated using a non-deterministic minimisation algorithm to ensure treatment concealment and balanced allocation across the two treatment groups for site and by age group. The service may be accessed via the secure randomisation
website (24 hours/7 days a week).

The patient, local investigator and all study and project management staff will be blinded as to treatment allocation. The statistician will have access to the unblinded code. The site pharmacist will have access to the treatment allocation in order to make up the active drug/placebo.

The RRAMP provides a facility for emergency unblinding of treatment allocation which can be accessed by the local principal investigator. All emergency unbinding will be at the discretion of the local investigators, when clinically indicated for the safety of the patient. Investigators should refer to the standard operating procedures (SOP) for the emergency unblinding procedure provided in the Investigator Site File. Non-emergency unblinding can be requested via the RRAMP system, and will require approval by the Chief Investigator.

## Trial procedures

The study procedures are reported in detail in
Table 3. Each participant will be involved in the trial for 13 months, and this includes: Screening phase (1 month), exposure to active drug/placebo (6 months), post-end of treatment follow-up (6 months).

**Table 3. T3:** Schematic representation of assessments at study visits.

	Screening Visit 1	Baseline Visit 2	Visit 3	Visit 4	Visit 5	Visit 6	Visit 7
Day	-1 to-30	0	30	60	90	180	360 Or at study end
Month			1	2	3	6	12
Time window			+/- 7 days	+/- 7 days	+/- 7 days	+/- 7 days	+/- 7 days
**Informed consent**	x						
**Review inclusion/exclusion criteria**	x	x					
**Medical & family history**	x						
**Randomisation**		x					
**Aldesleukin/ Placebo administration**		x ^a^ Twice-weekly, three days apart – with FU call daily for first week					
**Patient AE diary**		Twice-weekly, between treatments. Completed by patient/family at home					
**Provide instructions for DBS at home** **and provision of Ensure Plus**		x					
**Twice-weekly home visits from nurse**		Twice per week to deliver IMP and provide Ensure, if needed.					
**Concomitant medications**	x	x	x	x	x	x	x
**Height, weight and BMI**	x	x	x	x	x	x	x
**Pubertal stage**	x						
**Physical examination**	x	x	x	x	x	x	x
**Vital signs (temperature, Heart rate,** **blood pressure)**	x	x	x	x	x	x	x
**Serum**		x				x ^b^	x
**Random C-peptide (venous)**	x						
**HbA1c (local)**		x ^e^			x	x	x
**HbA1c (central)**		x			x	x ^b^	x
**PBMC**		x	x		x	x ^b^	x
**Treg levels**		x	x	x	x	x ^b^	x
**TBNK FACS assay**		x	x	x	x	x ^b^	x
**DBS for C-peptide ^c^**		weekly at home				Monthly until study end	
**Full blood count ^d^**	x		x	x	x	x	
**Liver function tests ^d^**	x		x	x	x	x	
**Renal function tests ^d^**	x		x	x	x	x	
**Electrolytes ^d^**	x		x	x	x	x	
**Thyroid function ^d^**	x				x	x	
**Pregnancy test (post-menarcheal girls)**	x	x	x	x	x	x	
**Insulin dose data**		x	x	x	x	x	x
**Adverse events review**		x	x	x	x	x	x

AE: adverse event; BMI: body mass index; HbA1c: haemoglobin A1c; IMP: investigational medical product; PBMC: Peripheral blood mononuclear cells; TBNK FACS: T-cell, B-cell and NK cell Fluorescence activated cell sorting; Treg: T regulatory cells
^a^ Treatment should start on day of randomisation or within 7 days thereafter. First dose of IMP or placebo should be given in a hospital setting and the patient observed for a period afterwards. All subsequent doses are administered at home by the research nurse, twice-weekly, three days apart. Wherever possible, doses should be taken on the same days each week e.g. Tuesday and Friday or Monday and Thursday.
^b^should be taken before final injection.
^c^DBS will be also collected at home every week in-between monthly visits until 6 months post treatment start, and then monthly from 7–12 months. Samples should always be taken prior to administration of study drug. The first at-home DBS will be supervised by a research nurse.
^d^Local results may be used if available, and taken within 2 weeks of the visit, or within 4 weeks of the screening/baseline visit.
^e^This should be local HbA1c data, either from point of care (finger prick), or venous samples

## Screening (Visit 1)

Patients need to start screening within 6 weeks of diagnosis of T1D.

Patients will attend an approved participating site for screening within 30 days prior to administration of the first dose of the study medication (Day 1). Screening, randomisation and first dose of trial treatment must be carried out within 10 weeks of diagnosis (
Figure 1).

**Figure 1. f1:**
[figure not shown]
Screening, randomization and treatment start.

Assessments performed at screening are as follows: review of inclusion/exclusion criteria, collection of medical history, physical examination (general appearance, cardiovascular system, respiratory system, gastrointestinal system, skin appearance), collection of information on family history and concomitant medications; assessment of height, weight, BMI, pubertal stage, vital signs (temperature, heart rate (HR), blood pressure (BP). Blood samples will be collected for measurement of: C-peptide, full blood count, liver function tests (aspartate transaminase, alanine aminotransferase, total bilirubin, alkaline phosphatase, gamma-glutamyl transferase), renal function tests (creatinine and urea), electrolytes, thyroid function tests (TSH, FT4). A pregnancy test (urine) will also be performed for females of childbearing potential, following menarche.

## Baseline assessments for those who are eligible and have consented (Visit 2)

Following screening, a baseline assessment will be performed and this will include: review of inclusion/exclusion criteria, collection of data on concomitant medications, insulin dose; randomisation; physical examination; assessment of height, weight, BMI, vital signs, blood samples for HbA1c, peripheral blood mononuclear cell (PBMC), TBNK FACS (T-cell, B-cell and NK cell Fluorescence activated cell sorting); DBS for measurement of C-peptide.

At the baseline visit, participants will also be provided with instructions on how to collect DBS for C-peptide weekly at home, including a record of finger prick blood glucose measurements, during the trial period. In addition, they will be provided with: 1) adverse events (AE) diaries and instructions on how to complete them (see extended data
^36^); 2) Ensure Plus liquid meals, or list of standardised breakfasts (see extended data
^36^). Where appropriate, contraceptive advice will be also provided, and a pregnancy test performed.

## Beginning of treatment

Treatment can start on the day of randomisation (visit 2) and should start no later than 7 days after randomisation. Participants will be asked to attend the designated clinical research facility or the hospital site to receive their first injection of aldesleukin or placebo.

Study participants will be observed in the clinical research facility or hospital setting for 2 hours post administration. Participants who experience any adverse event after study drug administration will be directly observed for a further 2 hours or until all symptoms and signs have resolved.

## Subsequent assessments

All subsequent assessments will be performed at the study sites. Assessments will be scheduled to occur ideally on day 3 following the latest injection.

Participants will undergo standard study visits after 1, 2, 3, 6 months from the beginning of treatment (study visits 3 to 6). Each study visit will include: recording of concomitant medications and insulin doses; review of any AE; physical examination; assessment of height, weight, BMI, vital signs (temperature, HR, BP); collection of blood samples for measurements of PBMC, Treg levels, TBNK FACS assay, full blood count, liver function and renal function tests, electrolytes; pregnancy test (where indicated). Additional serum samples will be taken and stored for future analyses. At visit 5 and 6, HbA1c and thyroid function will be also assessed.

For all visits, if there are local blood tests that have been performed as part of standard of care within the two weeks prior to the trial visit, the results of these may be used instead of taking additional samples for trial purposes.

For all visits, if the visit coincides with treatment injection, all blood samples (including DBS sample) should be taken before the injection.

## In between study visits

There will be daily telephone contact with study participants initially for the first week after treatment start and then contact will be via the twice-weekly nurse visits.

In between study visits participants will collect weekly home DBS to measure C-peptide, before and after a liquid meal or standardised breakfast.

A patient AE diary will need to be completed by the participants/their family, twice a week, between treatments, for the duration of their treatment.

### Collection of home dried blood spots

Instruction, both oral and written (provided as extended data
^36^), will be given to participants/parents at the baseline visit about collection of DBS samples at home between hospital visits, and in the first week of treatment, the research nurse will provide further instruction on the DBS collection and the DBS collection will be supervised by them, where possible. Copies of instructions will be provided in the investigator site file.

DBS sampling will be done once a week (+/- 2 days), (before and after a liquid meal or standardised breakfast) from baseline until treatment end at 6 months, and then monthly up to 12 months, for the measurement of C-peptide. If the DBS sample is taken on a treatment day, then the sample must be taken before treatment is given.

DBS samples and blood glucose measurements will be taken fasting immediately before a standardised meal (the first meal of the day), consisting in the Ensure Plus drink, and at 60 minutes from the start of consuming the drink, by finger prick in the home setting. If blood glucose is not between 4 and 11.1 mmol/l, they should take the DBS samples on another day. Participants who are not able to tolerate Ensure Plus will be advised to eat a standardized breakfast with a defined content of carbohydrates, proteins and lipids, which will need to be the same for all DBS collections during the study. Details are provided in the Investigator Site File.

Participants will be asked to withhold their pre-breakfast insulin until after the post-prandial DBS samples have been taken so as not to interfere with the C-peptide result. Following the 60-minute DBS sample, the patient will give a correction dose either via injection or pump, according to the patient’s own insulin sensitivity factor.

The completed DBS card will then need to be air dried for 24 hours before being posted to the laboratory in the pre-paid envelope provided.

DBS collection can be facilitated, when possible, by the research nurses during their twice-weekly home visits to dispense aldesleukin/placebo. Reminders to patients to do the DBS will be provided by the research nurses at their visits. Reminders post-treatment will be given by site staff at participating study sites via a text message or telephone call.

### Adverse events diaries

Participants/parents will be asked to complete AE diaries at home during the treatment period, to monitor AEs associated with the trial treatment.

The diaries should be completed twice a week, between treatments, for the whole 6-month duration of the trial. One questionnaire covers eight injections (approximately one month of treatment).

Paper rulers will be provided in the Investigator Site File that can be given to the families to facilitate measurement of injection site reactions. Completed diaries can be given to research nurses during their visits or can be brought to the next study visit at hospital.

### End of treatment and long-term follow-up assessments

Subjects will be followed up for six months after the end of the 6-month treatment period and during this period they will be asked to collect monthly home DBS to measure C-peptide, before and after a liquid meal or standardised breakfast.

At the end of the 6-month post-treatment follow-up period a formal assessment will be repeated: record of concomitant medications and insulin doses; AE review; physical examination, assessment of height, weight, BMI, vital signs (temperature, HR, BP); collection of blood samples for HbA1c, PBMC, Treg levels, TBNK FACS assay, additional serum samples.

There will be no treatment with aldesleukin after the end of the study. Patients enrolled into this study will already be receiving the appropriate standard of care, and this care will be continued at the end of the study.

### Early discontinuation/withdrawal of participants

During the course of the trial participants or their parents/guardians may choose to withdraw early from the trial treatment at any time. This may happen for a number of reasons, including but not limited to: 1) The occurrence of what the participant perceives as an intolerable AE; 2) Inability to comply with trial procedures; 3) Participant decision. Participants may choose to stop treatment but may remain on study follow-up. Participants may also withdraw their consent, meaning that they wish to withdraw from the study completely. Under these circumstances, the site needs to document all relevant discussions in the patient notes and notify the Trial Office, which will allow the office to mark all future electronic case report forms (CRFs) as not applicable.

Under these conditions, investigators are still responsible to follow up any serious adverse event (SAEs) until resolution. Data collected up to the time of consent withdrawal will be used in the analysis. No further data or samples would be collected after withdrawal.

In addition, the Investigator may discontinue a participant from the trial treatment at any time for any reason including, but not limited to: 1) Pregnancy; 2) Ineligibility (either arising during the trial or retrospectively having been overlooked at screening); 3) Significant protocol deviation; 4) Significant non-compliance with treatment regimen or trial requirements; 5) An AE which requires discontinuation of the trial medication or results in inability to continue to comply with trial procedures; 6) Disease progression which requires discontinuation of the trial medication or results in inability to continue to comply with trial procedures

The type of withdrawal and reason for withdrawal will be recorded in the CRF.

If the participant is withdrawn due to an AE, the Investigator will arrange for follow-up visits or telephone calls until the adverse event has resolved or stabilised.

If a participant is withdrawn from treatment due to pregnancy, the pregnancy will be followed up to outcome.

Any parents or guardian of the participant or the participant requesting to withdraw from intervention will be asked if they want to continue to attend study visits and to complete all study assessments. If they agree then they will be put on to the post-treatment follow-up schedule of monthly DBS and a final visit after 6 months of follow up. During this time all participants will continue to receive the same level of supervision as received by other study patients.

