## Protocol

### Objectives

The Primary Objective of the
**I**nterleukin-2
**T**herapy of
**A**utoimmunity in
**D**iabetes (ITAD) trial is to assess the effects of ultra-low dose aldesleukin administration on endogenous β-cell function, as measured by weekly assessments of fasting and post-prandial C-peptide from DBS in children and adolescents with newly diagnosed T1D.

The Secondary Objectives are: 1) To assess the efficacy of regular dosing of aldesleukin in increasing Treg levels; 2) To confirm the clinical safety and tolerability of ultra-low dose aldesleukin; 3) To assess changes in the immune system indicating benefit or potential risk for future gains/loss in β-cell function and immune function; 4) To assess treatment effect on glycaemic control.

Table 1 reports the trial objectives and related outcome measures.

**Table 1. T1:** Study objectives and outcomes.

Objectives	Outcome Measures	Timepoint(s) of evaluation of this outcome measure
**Primary Objective** To assess the effects of ultra-low dose aldesleukin administration on endogenous beta-cell function as measured by frequent home dried blood spot (DBS) fasting and post-prandial C-peptide in children and adolescents with newly-diagnosed type 1 diabetes (T1D).	Differences in slopes of dried blood spot (DBS) C-peptide over the 6 month-treatment period between the active and placebo groups.	Weekly DBS C-peptide collected during the 6-month treatment period, and then monthly during the 6 months of follow-up
**Secondary Objectives** 1) To assess the efficacy of regular dosing of aldesleukin in increasing T-regulatory (Treg) levels	1) Change in Treg, Teff and NK56 ^bright^ cell frequencies from baseline	1) At baseline and then 1, 2, 3, 6 and 12 months from the beginning of treatment
2)To confirm the clinical safety and tolerability of ultra-low dose aldesleukin	2) Safety will be assessed at each visit by: • Physical examination, including assessment of the most commonly reported reactions to low- or high-dose aldesleukin, namely influenza-like syndrome, skin reaction, diarrhoea, nausea; vital signs (temperature, blood pressure, heart rate); weight, abnormal laboratory parameters (liver, kidney function, full blood count); reporting of adverse events.	2) At screening, baseline and then 1, 2, 3, 6 and 12 months from the beginning of treatment

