### Expected Adverse Reactions (AR)/Serious dverse reactions (SARs)

All expected ARs are listed in the reference safety information, Section 4.8 of the current, approved SmPC
^38^. This must be used when making a determination as to the expectedness of the AR. If the AR meets the criteria for seriousness, this must be reported following the specific requirements.

The relationship of each AE to the trial medication must be determined by a medically qualified individual according to the following definitions:

a) Related: The adverse event follows a reasonable temporal sequence from trial medication administration. It cannot reasonably be attributed to any other cause.

b) Not Related: The AE is probably produced by the patient’s clinical state or by other modes of therapy administered to the patient.

Expectedness will be determined according to the reference safety information, Section 4.8 of the current, approved SmPC.

All AEs occurring during the trial, from randomisation until 30 days after completion of trial treatment, that are observed by the Investigator or reported by the participants, parent/guardian will be recorded on the CRF, whether or not attributed to trial medication.

Clinicians, during the clinic visit AE review, should at a minimum assess: IMP/placebo injection sites (redness, swelling, nodule, and pain), episodes of high temperature, loss of appetite, diarrhoea, nausea, vomiting, reduced activity, chills, headache, and muscle pain.

The following information will be recorded: description, date of onset and end date, severity, assessment of relatedness to trial medication, other suspect drug or device, and action taken. Follow-up information should be provided as necessary.

The local Principal Investigator (or other delegated member of the study team) will review each AE to assess and document the severity of the impact of the event. The severity of events will be assessed on the following scale: 1 = mild, 2 = moderate, 3 = severe.

It will be left to the Investigator’s clinical judgment to decide whether or not an AE is of sufficient severity to require the patient’s removal from treatment. A participant, or his/her parent/guardian, may also voluntarily withdraw from treatment due to what he or she perceives as an intolerable AE. If either of these occurs, the participant must undergo an end of trial assessment and be given appropriate care under medical supervision until symptoms cease, or the condition becomes stable.

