## Statistics

### Description of statistical methods

Full details of the statistical analysis will be detailed in a separate statistical analysis plan (SAP) which will be drafted early in the trial and finalized prior to the primary analysis data lock.

Descriptive statistics will be used to describe the demographics between the treatment groups. The primary outcome is change in DBS C-peptide (slopes) during the 6-month treatment period. This will be analysed using Analysis of Covariance (ANCOVA) with adjustment for stratification factors (site, age group) and baseline C-peptide values. Between group differences with corresponding 95% confidence intervals will be reported. If not normally distributed, non-parametric methods will be used with no adjustment (for example the Mann-Whitney Test or Kruskal-Wallis test).

Standard statistical tests will be used to compare the actively treated group with the placebo group (t test, Mann Whitney U-test, analysis of covariance, chi square test), with P values below 0.05 indicating significance.

The incidences of adverse events will be reported and, where appropriate, the two groups will be compared with the use of a logistic regression model.

Analyses will be undertaken on an intent to treat population (all patients analysed as randomised) with sensitivity analyses undertaken to explore deviations from the protocol and compliance with treatment.

An interim analysis based on safety measures is planned for the age-based step-down approach. The plan is to expose to treatment firstly six participants in the age group 12–18 years for a minimum of one month. If after review of the unblinded external safety data and satisfactory safety is established, recruitment will be extended to the younger age group, 6–11 years.

Stata (StataCorp LP) or other appropriate validated statistical software will be used for analysis.

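### Families who stop injections but agree to full follow-up are moved to monthly DBS and one final visit, so the measurement schedule depends on staying on treatment

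*Protocol article*

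**What the plan says.** The protocol article separates stopping treatment from leaving the trial. Early discontinuation/withdrawal of participants says "Participants may choose to stop treatment but may remain on study follow-up" and treats withdrawal of consent as a different event. Families requesting to stop the intervention "will be asked if they want to continue to attend study visits and to complete all study assessments". If they agree, "they will be put on to the post-treatment follow-up schedule of monthly DBS and a final visit after 6 months of follow up". The section End of treatment and long-term follow-up assessments gives that schedule monthly DBS and a single formal assessment at its end, with no other visit.

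The outcomes run on another clock:

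- **Primary outcome** (Objectives, Table 1): "Differences in slopes of dried blood spot (DBS) C-peptide over the 6 month-treatment period between the active and placebo groups".
- **DBS schedule** (Trial procedures, Table 3, note c): collected "every week in-between monthly visits until 6 months post treatment start, and then monthly from 7–12 months". Collection of home dried blood spots instead ties weekly sampling to the end of treatment, placed at 6 months.
- **Secondary outcomes** (Table 1): Treg, TBNK, insulin dose and safety at months 1, 2, 3, 6 and 12 from the beginning of treatment; HbA1c at months 3, 6 and 12.
- **Analysis** (Description of statistical methods): "Analyses will be undertaken on an intent to treat population (all patients analysed as randomised").

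For a child who leaves treatment because of an adverse event, the section on expected adverse reactions adds that "the participant must undergo an end of trial assessment and be given appropriate care under medical supervision".

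**The concern.** An intention-to-treat comparison needs outcomes measured in the same way whether or not treatment continues. Here stopping injections, a post-randomisation event, changes how often the primary measure is taken and removes visits at which secondary outcomes are due. This applies to families who have just agreed to do everything, so the loss comes from the protocol and not from refusal.

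Stopping may differ by arm, for instance through injection-site reactions. The month 3 and month 6 comparisons of Treg, TBNK and insulin dose, and of HbA1c, would then lean towards children still on treatment while being labelled intention to treat. A later analysis plan can model missing visits, but it cannot recover visits that were never scheduled.

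**Working it through.** **1. The plan's own figure.** Power calculation gives 24 active and 12 placebo, slope difference 0.53, SD 0.523. A two-sample equal-variance t-test at two-sided 0.05 (sidedness assumed) has 79.5% power, and 36 × 1.25 = 45. The stated size reproduces, and the point does not alter it.

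**2. Effect on one child's slope.** Inputs: weekly DBS at weeks 0 to 26, which is 27 occasions (Table 3, note c); after a stop, one sample per month (Early discontinuation/withdrawal of participants). A month is taken as 52/12 = 4.33 weeks. Assumptions: straight-line slope by least squares, independent errors, full compliance.

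The within-child error variance of the slope is σ²/S, with S = Σ(t − t̄)². On the full calendar, S = 27 × (27² − 1)/12 = 1638. The variance ratio after a switch is 1638/S.

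Example, stop at week 13: samples at weeks 0 to 13, then 17.33, 21.67 and 26. That is 17 occasions with mean 156/17 = 9.18 and S = 833.4. The ratio is 1638/833.4 = 1.97.

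| Stop at month | Weekly samples to stop | Later samples to week 26: monthly (weekly if calendar kept) | Total of 27 | S | Variance ratio | SE ratio | Final visit (stop + 6 months) |
|---|---|---|---|---|---|---|---|
| 1 | 5 | 5 (22) | 10 | 785.6 | 2.09 | 1.44 | month 7 |
| 2 | 9 | 4 (18) | 13 | 819.2 | 2.00 | 1.41 | month 8 |
| 3 | 14 | 3 (13) | 17 | 833.4 | 1.97 | 1.40 | month 9 |
| 4 | 18 | 2 (9) | 20 | 917.1 | 1.79 | 1.34 | month 10 |
| 5 | 22 | 1 (5) | 23 | 1115.3 | 1.47 | 1.21 | month 11 |

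A stop at exactly week 8 also leaves 13 of 27 occasions (S = 763.2, ratio 2.1).

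The ratio is sensitive to how the end of the window is handled. For a stop at week 9, monthly samples fall at weeks 13.33, 17.67 and 22, so a hard cut at week 26 gives S = 520.1 and a ratio of 3.15. Admitting the next sample, at week 26.33, gives S = 848.1 and 1.93. Ratios near 3 therefore depend on the cut-off convention and are not used as the size of the effect.

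**3. Effect on the visits.** For a stop just after the month's visit, if there is one:

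- Month 1: visits at months 2, 3 and 6 are no longer scheduled.
- Month 2: months 3 and 6 are lost.
- Month 3, 4 or 5: month 6 is lost.
- In every case the final visit falls at a time that is neither month 6 nor month 12 in Table 1.

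**4. From one child to the trial.** The variance of a child's estimated slope is σ_b² + σ²/S, where σ_b² is the true spread of slopes between children. The ratios in step 2 apply only to the second term. The documents give neither the split behind the SD of 0.523 nor the number of children who will stop but stay, so no trial-level power loss can be computed.

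**The case against.** The strongest reply is that DBS is thinned and not stopped. Monthly spots continue through month 6, so every child who agrees still contributes a 0-6 month slope. A doubled within-child error variance is not a doubled variance of the treatment comparison. The protocol also plans intention to treat, investigation of missingness, multiple imputation where appropriate, and sensitivity analyses. All of this stands for the primary outcome, where the main cost is precision. One residue remains: an unweighted ANCOVA of per-child slopes would treat a sparse slope as equal to a weekly one. The reply does not cover the secondary outcomes, whose visits are simply not scheduled, though a child who stops after month 3 already has the visits up to that point.

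Four stronger readings are tempting, and the documents do not support them:

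- **Outcome collection ends when a child stops for an adverse event.** If so, the variance ratio would be about 27 for a stop at month 2 and 164 at month 1. But the text requires an assessment and does not say that collection then ends, while the withdrawal section allows continued follow-up. The wording is unclear; it is not a rule that truncates the data.
- **About 9 of 45 children are affected.** The increase from 36 to 45 covers dropouts and extended periods off treatment. It does not count children who stop but stay. Planned treatment breaks do not trigger the switch, and children who withdraw consent give no further data under any schedule.
- **Worsening disease triggers the reduced schedule.** "Disease progression which requires discontinuation of the trial medication" is on the list of reasons for which the investigator may discontinue treatment. The switch is stated for participants or parents who ask to stop.
- **The primary analysis is irreparably biased.** The spots are still collected through month 6, so the text does not show this.

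**Conclusion.** The point holds in limited form. The protocol states a rule that makes the measurement schedule depend on staying on treatment, and the rule conflicts with its own DBS calendar, its fixed outcome times and its intention-to-treat analysis. It is also at odds with itself, since families who agree to all assessments are then scheduled for fewer.

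For the primary outcome the cost per affected child is about 1.5 to 2.1 times the within-child error variance, on the assumptions in the working and for stops at whole months. The more serious harm is to the secondary outcomes: unscheduled month 1-6 visits, depending on when the child stops, and a final visit at about months 7-11. The latter rests on reading the 6 months of follow-up as counted from stopping. How much this matters for the trial depends on how many children stop but stay, which the documents do not give.

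**What to change.** In Early discontinuation/withdrawal of participants, replace the switch to the post-treatment schedule with this: every child who stops injections without withdrawing consent stays on the original calendar counted from treatment start, as far as the family agrees. That means weekly DBS to month 6, visits at months 1, 2, 3 and 6, monthly DBS to month 12, and the month 12 visit.

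Align Table 3, note c, and Collection of home dried blood spots, so that weekly sampling is tied to 6 months from treatment start in both. Reconcile the end-of-trial assessment in the adverse-reactions section with the continued follow-up in the withdrawal section, so that sites do not read it as ending outcome collection.

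The cost is a protocol amendment and a change to the CRF schedule; the sample size is unchanged. Families who stopped carry more burden: by the table above, 17, 14, 10, 7 or 4 extra DBS occasions up to week 26 for a stop at month 1, 2, 3, 4 or 5, plus the restored visits. Because nurse visits to give injections would end, reminders would go by text or telephone, as the protocol already does after treatment.
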